## Abstract

**Background:**

Chronic childhood malnutrition, as manifested by stunted linear growth, remains a persistent barrier to optimal child growth and societal development. Environmental enteric dysfunction (EED) is a significant underlying factor in the causal pathway to stunting, delayed cognitive development, and ultimately morbidity and mortality. Effective therapies against EED and stunting are lacking and further clinical trials are warranted to effectively identify and operationalize interventions.

**Methods/design:**

A prospective randomized placebo-controlled parallel-group randomized controlled trial will be conducted to determine if a daily supplement of lactoferrin and lysozyme, two important proteins found in breast milk, can decrease the burden of EED and stunting in rural Malawian children aged 12–23 months old. The intervention and control groups will have a sample size of 86 subjects each. All field and laboratory researchers will be blinded to the assigned intervention group, as will the subjects and their caregivers. The percentage of ingested lactulose excreted in the urine (Δ%L) after 4 h will be used as the biomarker for EED and linear growth as the measure of chronic malnutrition (stunting). The primary outcomes of interest will be change in Δ%L from baseline to 8 weeks and to 16 weeks. Intention-to-treat analyses will be used.

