### Outcomes and sample size

The primary outcomes of interest will be improvement of a major biomarker of EED, the percent of ingested lactulose excreted in the urine (Δ%L), from baseline to 8 weeks and to 16 weeks. Linear growth has been shown to best correlate with this component of the traditional dual-sugar absorption test [42]. The enrollment goal will be at least 86 subjects in each of two equally sized intervention or control groups. This sample size was chosen to detect a decrease of 0.05% in Δ%L between the two groups (considered to be a clinically significant improvement in gut barrier function) with an alpha value of 5% and 90% power. This assumes that urinary lactulose measurements will be distributed similarly to prior studies that showed that more than 80% of apparently healthy rural Malawian children had EED. Additional children will be enrolled to account for children who drop out or are excluded during the course of the study, as well as for some children who will not have a satisfactory data collection due to technical issues with the urine collection. The differences in lactulose recovery before and after the intervention will be calculated and compared between the intervention and control groups using *t* tests if the data are normally distributed or the non-parametric Wilcoxon Rank Sum Test if the data are not normally distributed.

Secondary outcomes of interest include linear and ponderal growth, adverse gastrointestinal symptoms, and any side effects due to the interventions. Linear growth will be calculated as the change in length over time, expressed as mm/day. Weight change will be calculated as the change in weight over time, normalized to the enrollment weight, and expressed as g/kg/day. Exploratory analyses of mRNA markers of intestinal inflammation found in the stool will also be conducted as part of our ongoing investigations into identifying novel biomarkers for EED [43, 44].

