### Data management and analysis

Clinical data focusing on demographic and anthropometric values will be collected on standardized forms by field workers. Data will be double-entered into a password-protected Microsoft Access database by research assistants blinded to the intervention assignment. All discrepancies will be resolved by examination of the original forms and discussion with the relevant field workers. After entering all data and resolving inconsistencies, the data set will be locked. For anthropometric values, comparisons will be made between the lactoferrin-lysozyme mixture and the control rice flour groups. Fisher’s exact test will generally be used to compare discrete parameters, and Student’s *t* test will be used for continuous parameters. A difference with *P* < 0.05 will be considered statistically significant. These statistical methods will also be used for all clinical data and EED measures.

All trial data, including personal information, will be kept in password-protected encrypted computer databases on password-protected computers. Paper records will be kept in locked file cabinets and the research team’s headquarters in locked buildings. Given the relatively short duration of the study and the need to analyze all urine concentrations simultaneously at the end of the study, no interim analyses are planned and no stopping guidelines have been established. The full protocol, participant-level dataset, and details of all statistical analyses will be made available to any interested parties after the conclusion of the trial by contacting the principal investigators.

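### Two unordered primary outcomes (weeks 8 and 16), each tested at P < 0.05, do not deliver both the stated 5% alpha and the stated 90% power

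*Protocol article*

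**What the plan says.** - **Two primary outcomes.** The Abstract (Methods/design) says "The primary outcomes of interest will be change in Δ%L from baseline to 8 weeks and to 16 weeks". The section Outcomes and sample size repeats the plural and the same pair of time points, "from baseline to 8 weeks and to 16 weeks". Neither place ranks them.
- **One sample-size calculation.** The same section says "This sample size was chosen to detect a decrease of 0.05% in Δ%L between the two groups", "with an alpha value of 5% and 90% power", with the target "The enrollment goal will be at least 86 subjects in each of two equally sized intervention or control groups". The calculation is attached to neither visit.
- **One test sentence.** "The differences in lactulose recovery before and after the intervention will be calculated and compared between the intervention and control groups", by t test or Wilcoxon rank sum test. It does not say which post-baseline visit is meant. Week 8 falls in the middle of the 16-week intervention.
- **One threshold.** Data management and analysis says that a difference with P below "0.05 will be considered statistically significant". Its next sentence extends the methods of that paragraph to all clinical data and EED measures. Urinary lactulose recovery is the EED measure, so the threshold covers both primary comparisons.

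The article gives no order, no division of alpha, and no rule on whether one or both comparisons must succeed.

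**The concern.** Alpha and power are properties of a decision rule. The article gives them for a single test, then names two primary tests without saying how they combine into one conclusion. If a significant result at either visit supports the claim, the trial has two chances of a false positive, each at 5%. If both visits must be significant, it has two chances to miss a real effect, each at 10%.

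A split result, with one visit significant and the other not, is quite possible. The text gives no basis for calling such a trial positive or negative, so the rule could be chosen after both results are known. What is at stake is the trial's main conclusion.

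**Working it through.** **Inputs.** From Outcomes and sample size: difference 0.05 percentage points, alpha 5%, power 90%, 86 per group. From Data management and analysis: P < 0.05 per comparison. Assumed, because not stated: two-sided tests, the same SD and the same full effect at both visits, and a correlation r between the two change scores, shown as a range.

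**1. The plan's own figure.** For one two-sided comparison of means, n per group = 2 (z₀.₉₇₅ + z₀.₉₀)² (SD/δ)². No SD is given (the text says only "This assumes that urinary lactulose measurements will be distributed similarly to prior studies"), so 86 cannot be reproduced independently. Solving backwards:

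(SD/δ)² = 86 / [2 × (1.960 + 1.282)²] = 86 / 21.01 = 4.09, so SD = 2.023 × 0.05 = 0.101.

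With that SD, 86 per group gives exactly 90% for a single unadjusted test (standardised difference 0.494; 0.497 with the t distribution). The figure fits one test. The steps below do not depend on the SD itself, only on 86 per group giving 90% at two-sided 5%.

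**2. Correlation of the two changes.** Both changes subtract the same baseline. With equal variances σ² and an equal correlation ρ between all visits, the covariance of the changes is σ²(1 − ρ) and each variance is 2σ²(1 − ρ), so r = 0.5 whatever ρ is.

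**3. Either visit suffices.** Type I error = 1 − P(|Z₁| ≤ 1.96 and |Z₂| ≤ 1.96), bivariate normal with correlation r. For r = 0 this is 1 − 0.95² = 0.0975.

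**4. Both visits required.** Each statistic has mean 1.960 + 1.282 = 3.242 and misses with probability 0.10. Power = 1 − 2 × 0.10 + P(both miss). For r = 0 this is 0.80 + 0.01 = 0.81; for r = 0.5 it is 0.80 + 0.032 = 0.832.

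| r | Type I error, either suffices | Power, both required |
|---|---|---|
| 0 | 9.75% | 81% |
| 0.3 | 9.5% | 82% |
| 0.5 | 9.1% | 83% |
| 0.7 | 8.3% | 85% |
| 0.8 | 7.8% | 86% |
| 0.9 | 7.0% | 87% |

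To restore 90% when both are required takes 106 evaluable per group at r = 0, 103 at r = 0.5 and 98 at r = 0.8 (105.6, 102.4 and 97.6, rounded up).

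**5. Bonferroni (2.5% per visit).** Power per visit = Φ(3.242 − 2.241) = Φ(1.00) = 84.1% (84.0% with the t distribution). To restore 90%: 86 × [(2.241 + 1.282) / 3.242]² = 86 × 1.181 = 101.6, so 102 evaluable per group.

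**The case against.** **Silence in a condensed article.** A testing order is often left to the full protocol or analysis plan, which the article says exists. That would dispose of a plain omission. Here, though, the article names two primary outcomes, sets an uncorrected threshold, extends it to the EED measures, and quotes alpha and power for one test. A nominal 5% is also the level used inside a fixed sequence or a both-must-succeed rule, so the threshold sentence does not exclude such a rule. But nothing in the text points to one, and a both-must-succeed rule would still miss 90%.

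**Each comparison alone is sound.** True: each has 5% alpha and 90% power taken singly. The two harms are also alternatives and must not be added. Under the either-visit rule only alpha fails; the chance of at least one success, with the full effect at both visits, is about 97% at r = 0.5. Under the both-visits rule alpha is at most 5% and only power fails.

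**The correlation may exceed 0.5.** If correlation fades with time, r = 0.5 × √[(1 − b)/(1 − a)], where a is the adjacent-visit and b the baseline-to-week-16 correlation. With a = 0.5 and b = 0.3 as an example, r = 0.59 and the type I error is about 8.8%. The inflation is then a little smaller, and it stays above 5% throughout the table.

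**More than 86 may be evaluable.** The target is a minimum and the randomisation list runs to 125 per group; if all 125 were evaluable, Bonferroni power per visit would be 95%. But the power statement is tied to 86, and the extra children are there to cover losses and failed urine collections.

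**The test sentence may mean week 16 only.** That is a fair reading of its wording, but it conflicts with the two primary outcomes named in the same section.

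**Conclusion.** The concern holds. With two co-primary time points, no available reading gives both 5% alpha and 90% power at 86 per group. If either visit can carry the claim, the type I error is about 9.1%, nearly double the stated level, and 7.0% to 9.75% over correlations from 0.9 to 0. If both are needed, power is about 83%, or 81% to 87% over correlations from 0 to 0.9. With a Bonferroni split, power per visit is 84%.

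These figures assume two-sided tests, 86 evaluable children per group giving 90% power for one test, and, for the power figures, the full effect at both visits. Because the SD is not stated, the 90% itself is taken from the article and not confirmed. The defect lies in the trial-level claim, not in either single comparison, and it should be settled before any primary result is seen.

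**What to change.** State one decision rule. The recommended one is a fixed sequence:

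- The single primary test is the change in lactulose recovery from baseline to week 16, the end of the intervention, compared between groups at two-sided 5%.
- The change to week 8 is tested at two-sided 5% only if week 16 is significant; otherwise it is reported descriptively.
- The test sentence in Outcomes and sample size names the visit, and the sample-size statement is attached to week 16.

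This holds the overall type I error at 5% and keeps 86 per group and the stated 90% for the first test. The chance of declaring both visits significant is the both-visits figure above, about 83% at r = 0.5. Nothing in the article ranks one visit above the other, so the order is the sponsor's choice; it only has to be fixed in advance.

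If the sponsor wants the two visits as equals, use Hochberg's procedure and restate the power. Per visit it lies between the Bonferroni 84% and the unadjusted 90%, because Hochberg rejects whenever Bonferroni does and never when that visit's P is 0.05 or more. If both must succeed, restate the target as about 98 to 106 evaluable per group (correlation 0.8 to 0).

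The fixed sequence costs one paragraph and no extra children. It can still be made without sight of results, since the article plans to analyse all urine concentrations together at the end with no interim analysis. The one real loss is that week 8 can no longer support the claim alone.

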**Discussion:**

A rigorous clinical trial design will be used to assess the biologically plausible use of lactoferrin and lysozyme as dietary supplements for children at high risk for EED. If proven effective, these safe proteins may serve to markedly reduce the burden of childhood malnutrition and improve survival.

**Trial Registration:**

Clinicaltrials.gov, NCT02925026. Registered on 4 October 2016.

**Electronic supplementary material:**

The online version of this article (doi:10.1186/s13063-017-2278-8) contains supplementary material, which is available to authorized users.

## Background

Undernutrition is directly or indirectly implicated in 45% of all deaths worldwide among children less than 5 years of age. Linear growth stunting is a common manifestation of prenatal and chronic early childhood undernutrition, afflicting at least 156 million children worldwide below 5 years of age. Stunting serves as a clinical marker for lifelong impairments in physical, immunological, neurocognitive, and socioeconomic potential. Although the prevalence of stunting is decreasing globally, it remains a significant problem and interventions to ameliorate stunting will be needed if the global community is to achieve the Sustainable Development Goals related to childhood health and nutrition [1]. Most of the irreversible stunting suffered by children in resource-limited settings occurs within the first 1000 days after conception, and is linked to pre-conception maternal nutritional status, nutrition and infections during pregnancy, postnatal nutrition, and gut health during this time [2]. Gut health, as defined here, is affected by nutrient intake and infectious assaults on the gut, and the inflammatory balance the gut must strike in optimizing the first while ameliorating the latter. Interventions to optimize gut health during early childhood are urgently needed in order to decrease the risk of stunting and subsequent morbidity and mortality. For the study presented here, we take the approach of improving the nutritional composition of complementary foods by supplementation with two compounds, lactoferrin and lysozyme, found in breast milk.

### Environmental enteric dysfunction

Environmental enteric dysfunction (EED) is a subclinical chronic inflammatory condition of the gut. Known in the past as tropical sprue, tropical enteropathy, or environmental enteropathy, it is condition that primarily affects rural, poor, but seemingly healthy children, most prominently below 2–3 years of age [3–5]. EED is histologically characterized by diffuse small bowel villous atrophy and T-cell infiltration of the intestinal mucosa that causes chronic immunostimulation [6], leading to increased intestinal permeability and impaired mucosal barrier function, which further leads to translocation of gut microbes and endotoxins, and nutrient malabsorption [7]. Although EED itself is a subclinical condition, affected children are subjected to increased rates of infection, poorer response to oral vaccines, and growth stunting.

Interventions aimed at combating EED have had mixed results. Trials involving antibiotics [8] and probiotics [9] to modulate the gut microbiota and decrease microbial-stimulated inflammatory responses have had limited success. Supplementation with multiple vitamin A [10], alanyl-glutamine [11], long-chain polyunsaturated fatty acids [12], albendazole [13], zinc [13], multiple micronutrient supplements [14], and mesalazine [15] have all been shown to at least transiently benefit small intestine function. However, these benefits have not always been consistent—even in combination—among children in the periods of highest food insecurity [16], and any demonstrated improvements in linear growth and development remain lacking. Given that malnutrition to this day still accounts for a significant amount of morbidity and mortality in children less than 5 years of age, interventions aimed at reducing EED are integral to improving child survival worldwide [17].

### Lactoferrin and lysozyme

Breastfeeding provides innumerable benefits to infants and children, both in the short and long term. Infants in low- and middle-income countries who have never breastfed are 14 times likely to die from all causes compared to exclusively breastfed infants in the first 5 months of life [18]; most of this benefit stems from a lower risk of acute infections.

Similar to children with minimal dietary diversity, breast milk has also been shown to be protective against increased intestinal permeability [19]. Lactoferrin and lysozyme are two proteins present in substantial concentrations within various human mucosal secretions, particularly breast milk [20]. Lactoferrin is an 80-kDa iron-binding glycoprotein which accounts for 25% of the protein in breast milk (1–3 g/mL) and functions to sequester iron, thereby inhibiting bacterial growth [19, 21]. Lysozyme is a 15-kDa protein present in breast milk at 0.1–0.3 mg/mL that acts as an antimicrobial by lysing a specific connection within the peptidoglycan layer of bacterial cell walls [22].

Previous research has demonstrated that both lactoferrin and lysozyme supplementation are safe and efficacious in children as young as 5 months of age [23]. Lactoferrin has been shown to improve hematocrit levels and decrease the rate of lower respiratory tract infections in neonates without adverse effects [24]. Lysozyme levels in breast milk have been positively correlated with neonatal weight gain [25].

Lysozyme has also been shown to modulate inflammatory response and gut structure, as well as alter microbiota in animal models. One study showed that pigs which were fed human lysozyme-enriched milk expressed significantly elevated blood levels of the anti-inflammatory cytokine transforming growth factor (TGF)-β1 and tended to have longer villi with thinner lamina propia, which are linked to increased intestinal surface area and increased nutritional absorptive capacity [26]. In this animal model, lysozyme also led to altered gut microbiota, relatively enriched in *Bifidobacteriacea* and *Lactobacillacea*, two populations associated with a healthy microbiome, and decreased *Mycobacteriaceae* and *Campylobacterales* populations, which are associated with disease [27, 28]. Another study of supplementation with transgenic milk containing human lactoferrin in malnourished pigs showed benefits to jejunal architecture, reduced intestinal permeability, and promotion of weight gain [29].

In combination, lactoferrin and lysozyme have been shown to work synergistically as bactericidal agents against both Gram-negative and Gram-positive bacteria. Lactoferrin destabilizes the outer membrane likely through a mechanism involving iron sequestration and binding to membrane lipopolysaccharide, while lysozyme acts on the inner peptidoglycan membrane [22, 30, 31]. Importantly, both are resistant to proteolytic degradation [32, 33], which is essential for any therapeutic use as an oral agent in humans.

In a study of Peruvian children between the ages of 5 and 33 months, supplementing oral rehydration solutions with lactoferrin and lysozyme in the setting of acute diarrhea with dehydration decreased the severity and duration of diarrheal episodes, without any adverse effects related to treatment [34]. These therapeutic properties make lactoferrin and lysozyme attractive candidates for the prevention and treatment of EED, and more broadly may be useful supplements for infants who cannot breastfeed or who are weaning from breast milk but may still benefit from their therapeutic properties.

### Study goals

There are numerous factors that contribute to stunting among impoverished children worldwide, poor gut health being among the most important. We plan to investigate the effect of nutritional supplementation with lactoferrin and lysozyme on the growth and gut health of children in rural Malawi, a setting where over 80% of children have EED [8, 9, 13, 14, 16, 35, 36].

## Methods/design

### Study design

This will be a prospective, randomized, double-masked controlled clinical trial to assess the effect of lactoferrin and lysozyme supplementation on growth and gut health in rural Malawian children. Children between the ages of 12 and 23 months will be eligible for enrollment, and those enrolled will receive the intervention daily for 16 weeks. A 1:1 allocation ratio will be used to assign children to either the intervention or placebo groups. The anticipated trial flow is depicted in Fig. 1. The Standard Protocol Items, Recommendations for Interventional Trials (SPIRIT) checklist is available as Additional file 1.

**Fig. 1 Fig1:**
[figure not shown]
Anticipated patient flow for the randomized clinical trial. *Defined as having weight-for-height *Z* score (WHZ) < –2, mid-upper arm circumference (MUAC) < 12.5 cm, and/or bilateral pitting edema suggestive of kwashiorkor

### Study setting

This study will enroll children in the villages surrounding the community of Mmwenye, Machinga District, Malawi. Most villagers work as subsistence farmers with maize as the primary crop. Water is primarily acquired from boreholes or carried by hand from nearby streams. Homes are generally small, with foundations constructed of mud brick and roofs of thatch or sheet metal. It is not uncommon for multiple generations to live within the same house. Defecation and urination are primarily done in the open [37] or for some families in pit latrines dug into the ground. Children interact frequently with farm animals including chickens, goat, and cattle, some of which are permitted within houses. Geophagy is common [38, 39]. Electricity, running water, and other utilities are generally absent; most cooking is accomplished on open wood or charcoal fires and most cleaning is performed at streams or with water obtained from those streams. Most household responsibilities and child-rearing are performed by women. It is common for women to marry and assume household responsibilities relatively early in life, and thus most women are illiterate and have not completed primary school. Most hospitals are situated in the larger cities and are therefore prohibitively far away from villagers; more commonly, local health clinics have only modest resources and staffing. Health promotion and disease prevention is primarily accomplished in the community by Health Surveillance Assistants (HSAs) [40].

